### Statistical methods

Categorical variables will be analyzed by descriptive statistics and presented as number of valid cases and percentage (%). Numeric variables will be analyzed as mean and standard deviation, median and interquartile ranges, or confident intervals. Since, it is possible that the patient population is quite different across the sites, analyses for the overall population will account for site differences or for the possibility of correlated observations within a site.

To compare adherence and outcomes over time (i.e., between years 1, 2 and 3) the following statistical approach will be applied: a) a test for normality in each category using the Shapiro-Wilks (<50 observations) or Kolmogorov–Smirnov, b) if normality assumption holds, a Welch’s F test will be done, c) if normality assumption still holds the ANOVA with post hoc Bonferroni will be performed. If the normality assumption is violated, a non-parametric test (Kruskal–Wallis) will be used to analyze categorical variables and for significant differences between the two groups (neurological vs clinical). A final *p* value of <0.05 will be considered statistically significant. Analysis of variability (distribution) per site for each variable of the 2 main outcomes will also be performed and Run Chart will be generated to follow the evolution of the outcomes over time for the 2 groups of patients: neurologic and clinical. All analysis will be done using the StataCorp. 2021. Stata Statistical Software: Release 17. College Station, TX: StataCorp LLC.

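### The year-by-year test sequence is mis-specified in two places: Kruskal–Wallis behind a normality check for categorical variables, and Welch's F as a step toward ordinary ANOVA

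*Protocol article*

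**What the plan says.** The protocol article, Statistical methods, sets out one chain of tests for the comparison over time: "To compare adherence and outcomes over time (i.e., between years 1, 2 and 3").

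- Step a: "a test for normality in each category using the Shapiro-Wilks (<50 observations) or Kolmogorov–Smirnov".
- Step b: "if normality assumption holds, a Welch’s F test will be done".
- Step c: "if normality assumption still holds the ANOVA with post hoc Bonferroni will be performed".
- Otherwise, where normality is violated: "a non-parametric test (Kruskal–Wallis) will be used to analyze categorical variables and for significant differences between the two groups (neurological vs clinical").
- Threshold: "A final *p* value of <0.05 will be considered statistically significant".

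For categorical variables the section otherwise gives only counts and percentages. It also promises that overall analyses will allow for site differences or within-site correlation. Box 2 lists the primary outcomes. They mix yes/no items (death, drug use, referral), counts (seizures, consultations, case discussions), durations (monitoring hours, length of stay) and two items on drug types (anticonvulsants; inotropes and fluid resuscitation).

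**The concern.** There are two separate faults.

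1. **Categorical variables.** Normality is not a property that a categorical variable can have or lack, so the check cannot route it anywhere. Kruskal–Wallis works on ranks. A set of drug types has no order, so its ranks come from whatever codes the database uses.
2. **Welch's F, then ANOVA.** Welch's F compares means without assuming equal variances. Its result carries no information on normality, so it cannot establish that normality still holds. Both tests address equality of the yearly means. No variance check chooses between them, and nothing says which p-value is reported. The second test also gives up the protection of the first.

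The Introduction hypothesises that adherence rises over time and outcomes improve, and this paragraph supplies the tests of change over time. A rule that allows two answers from the same data weakens any claim built on it.

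**Working it through.** **Inputs from the article (Sample size).** 3,240 eligible × 0.70 = 2,268 recruited; 2,268 / 3 = 756 per year. This reproduces the stated figures. (The 3,240 equals 18 × 5 × 36, whereas the 20 stated centres give 3,600. That is a separate matter, and nothing below depends on it.) The article gives no outcome rates, SDs or category counts, so those used here are assumptions.

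**1a. Yes/no outcomes.** With tie correction, H = χ² × (N − 1)/N. Both are referred to chi-square on 2 df, where p = exp(−statistic/2).

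- 756 per year, rates 10% / 8% / 6.5%: Kruskal–Wallis p = 0.03865, chi-square p = 0.03859.
- 756 per year, rates 40% / 36% / 33%: 0.01761 and 0.01758.
- 3,000 simulated null tables at 756 per year: largest difference in p 0.0002; both tests reject 5.2% of the time.

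**1b. One three-category variable.** Assumed: 200 treated infants per year, with types A/B/C split 120/40/40, 104/64/32 and 90/90/20. Column totals are 314, 194 and 92, so the expected yearly counts are 104.67, 64.67 and 30.67. Then χ² = 4.31 + 19.34 + 6.61 = 30.25 on 4 df, p = 4e-6. For Kruskal–Wallis only the type coded in the middle matters:

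- B in the middle: H = 2.34, p = exp(−1.17) = 0.31
- C in the middle: H = 17.80, p = exp(−8.90) = 0.00014
- A in the middle: H = 28.58, p = exp(−14.29) = 6e-7

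The same infants are significant or not at 0.05 according to the labels.

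**1c. The same table, one yes/no variable per type.** Kruskal–Wallis against chi-square:

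- Type A: H = 9.033 × 599/600 = 9.018; p = 0.0110 against 0.0109
- Type B: 6.4e-7 against 6.2e-7
- Type C: 0.0203 against 0.0202

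The arbitrariness disappears.

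**2. Welch's F and ANOVA under a true null.** Three normal groups, nominal 5%, 6,000 simulations per row. Year sizes and SDs are listed in the same order.

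| Year sizes | SDs | ANOVA | Welch's F |
|---|---|---|---|
| 756 each | 1 / 1 / 1 | 5.1% | 5.1% |
| 756 each | 1 / 1.5 / 2 | 5.3% | 4.9% |
| 500 / 756 / 1,012 | 2 / 1.5 / 1 | 9.3% | 4.7% |
| 500 / 756 / 1,012 | 1 / 1.5 / 2 | 3.3% | 5.1% |

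The unequal sizes sum to 2,268, the planned total. A second SD set (1.5 / 1.0 / 0.8) gave ANOVA 8.6% at sizes 600 / 840 / 1,080 (Welch's F 5.1%), 5.9% at 756 each and 3.5% with the sizes reversed. The 600 / 840 / 1,080 sizes sum to 2,520, more than planned; only their imbalance matters here.

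**3. How often the Welch/ANOVA branch is reached.** At 756 per year the stated normality check rejected in 100% of runs for the binary, count (Poisson, mean 2) and skewed (lognormal; gamma, shape 4) data tried. In a single centre, 756 / 20 is about 38 infants per year, and there the check rejected the gamma variable in only 52% of runs. The branch is therefore rare for pooled data but can be reached within centres.

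**The case against.** A reader might infer that p-values for most primary outcomes would be wrong or arbitrary. The article does not support that. For yes/no items Kruskal–Wallis gives practically the chi-square answer. For counts and durations it is a valid rank test, and for two groups it is the rank-sum test, so the neurological versus clinical comparison is sound for such outcomes.

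The drug-type example also rests on a coding that the article does not state. An infant may receive several drugs, and Outcomes promises n (%) or median [IQR], which fits one yes/no variable per drug. Under that coding the problem vanishes. This objection stands: the coding fault is conditional and reaches at most two Box 2 items.

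A second tempting reading is that ANOVA's error rate is inflated whenever yearly variances differ. It is not. With equal years the excess is small, and when the largest year has the largest SD the test is conservative.

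A third is that the switch at 50 observations sends one outcome to means in some centres and to ranks in others. The switch only selects which normality test is run. Differing normality results could still split centres, but how often depends on an assumed distribution, and dislike of normality pre-testing is largely a matter of preference.

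Finally, the stated aim is descriptive; percentages, per-site distributions and run charts are unaffected; and site adjustment and mixed models are already mentioned. That lowers the severity. It does not rescue the two rules, which are stated wrongly rather than left for a fuller plan.

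**Conclusion.** The point holds in limited form and should be fixed. The categorical rule is wrong in principle. In practice it is harmless for yes/no outcomes and serious only if drug types are analysed as a single multi-category variable, where the assumed example runs from 0.31 to 6e-7 on coding alone. The Welch-then-ANOVA rule is illogical and leaves the reported p-value undetermined. Its cost in error rate is about 9% or about 3.5% against a nominal 5% when both year sizes and SDs differ, depending on the direction, and about 6% at most in the equal-year settings tried. These sizes rest on assumed counts, SDs and yearly splits; the faults in the wording do not.

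**What to change.** Rewrite the paragraph on comparison over time:

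- Take categorical variables out of the normality and Kruskal–Wallis rule. Use chi-square or Fisher, or a logistic model with site, which meets the section's own promise on site differences.
- State that each drug type is analysed as its own yes/no variable.
- For comparisons of means, use Welch's F alone with a post hoc test that allows unequal variances, and delete the following ANOVA step.
- Keep Kruskal–Wallis for skewed numeric or count outcomes only.
- Fix one test per outcome in advance and use it in every centre.

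The cost is one reworded paragraph. No data item or sample size changes.

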### Missing data

As missing data can impact study validity by reducing sample size and statistical power of subgroup analyses, a comprehensive strategy was developed. First, missing data will be defined as values that are not available and that would be meaningful for analysis if they were observed. Second, the proportion of missing data for each variable will be presented. Furthermore, analysis to assess if patients with missing data differ from those with complete information for a given variable will be performed. Finally, information on why data are missing will be collected.

All efforts will be made to prevent missing data by a) collecting only critical data elements, b) focus on routinely collected data in real-world practice, c) develop completion guidelines, and d) perform pilot-test forms for the first 10 patients. Also, an ongoing data review in the CSI will be conducted for data completeness and quality. Moreover, investigators of each site will be trained on data collection and the importance of core data.

For analysis, we will understand the missing data, select the appropriate methodology (ies) for handling it and examine the sensitivity of different approaches. Thus, for each core variable we will generate frequency distributions and graphical displays. Two major methods will be used during analysis to handle missing data. For the primary analysis we are planning to perform a complete case analysis (use only cases with complete data) and them apply likelihood methods, i.e. mixed effect models to find the values of parameters which maximize the known likelihood value.

## Discussion

This large prospective, multicenter, and observational study will describe the use and adherence to a unique telemedicine neonatal neurocritical care guidelines and clinical outcomes. As a multidisciplinary approach to care for newborns with high-risk of brain injury has increased over the last 10 years, the implementation of an organized, low-cost, and high-expertise telemedicine guidelines has the potential to streamline clinical care improving outcomes.

The *PBSF Guidelines* defines high-risk neonates, with clear indications for neonatal neurocritical care. Among the etiologies associated with impaired neurodevelopmental outcomes, neonatal asphyxia represents the third cause of neonatal death worldwide (23%) [2, 3, 32–34]. In newborns with moderate or severe HIE the risk of death, cerebral palsy and/or disability among survivors is high. In addition, some disability might also occur in mild HIE infants [4, 6, 7, 35]. Neonatal seizures have been reported in approximately 3.5 per 1000 live births of term neonates [17] and several conditions are associated with increased risks for developing seizures such as perinatal asphyxia and ischemic stroke. Indeed, it is estimated that perinatal asphyxia is the leading cause of seizures in the neonatal period, accounting for 40 to 60% of all seizures in term newborns [36, 37]. Seizure burden is associated with more severe brain injury and worse neurodevelopmental outcomes after adjusting for underlying severity of brain injury. Status epilepticus is also associated with post neonatal epilepsy [17]. Since seizures are difficult to diagnose clinically, continuous monitoring by using aEEG, EEG or video aEEG/EEG will help the identification of sub-clinical events allowing immediate recognition and treatment, which can reduce seizure burden and improve neurodevelopmental outcomes [13–16].

Preterm infants are also at high risk for neurodevelopmental problems, and different areas may be affected such as neurosensory, cognitive, and behavioral functioning. The more immature, the greater the risks [8, 38] and extreme prematurity has been associated with moderate or severe neurocognitive deficits during childhood [39]. Moderate and late preterm infants (MLPT) can also have worse cognitive, language, motor development, social-emotional competence at 2 years of age when compared to term infants [40]. Other disorders such as cerebral malformations, infections, inborn errors of metabolism, and severe hemodynamic and ventilatory instability also carry risks of brain injury and seizures. Moreover, CHD affects from 4 to 75 per 1,000 live births and has been recognized as high risk for neurodevelopmental problems [41, 42]. In CHD, infants brain injury may follow episodes of cerebral hypoxia or hypoperfusion that can occur during the pre-, intra- and/or postoperative periods, in addition to biological and environmental factors [43–45]. Indeed, more than 50% of CHD patients have been reported with neurodevelopmental deficiencies [44–47] that may persist into adolescence [47]. All these situations are included as indications for the use of the *PBSF Guidelines*.

In recent decades, brain monitoring has become increasingly common in NICUs [48] but not yet a consolidated practice in all services, especially in low- and middle- income countries (LMIC), where the lack of structure, resources, and professional training is a major problem. Brazil is a large country with a population of > 200 million people and approximately 3 million births per year, with great financial disparity. This discrepancy directly affects the Brazilian health system, with differences in availability of financial, material, and personal resources, including adequate training of professionals. A prospective cross-sectional national survey conducted by our group evaluated the assessment of HIE and TH practices in Brazil. A total of 1,092 professionals answered and 62% reported using TH in their units. However only 13% received specific training for HIE assessment, 22% did not use any neurologic score, and only 12% had brain monitoring readily available, showing the need for well-established neurocritical care guidelines [31].

There are a variety of clinical applications of video aEEG/EEG monitoring and NIRS in neonates at high-risk for brain injury:

*Seizures*: clinical signs of seizures are easy to evaluate and overdiagnosis occurs frequently, resulting in unnecessary treatment [21, 33, 36]. Neonatal seizures are frequently underdiagnosed since more than 80–90% of seizures are subclinical, resulting in undertreatment. Indeed, the accuracy for seizure detection with clinical evaluation alone is < 9% [37]. New devices associate aEEG with raw EEG readings and even video imaging (video aEEG/EEG), providing higher accuracy for the detection of seizures [12, 36, 48, 49]. Shah et al. evaluated term newborns with clinical seizures monitored with aEEG with simultaneous continuous conventional EEG for seizure detection. In 41 non-status epilepticus seizures, 31 were correctly identified (sensitivity, 76%; specificity, 78%; PPV, 78%; NPV, 78%). However, they found a lower sensitivity (27–56%) when aEEG was assessed without the conventional EEG findings [11].*Hypoxic Ischemic Encephalopathy*: Three of the six major clinical trials of TH used an abnormal aEEG background activity as entry criteria [50–52]. Indeed, an abnormal aEEG may improve selection of neonates to be treated [53]. However, the presence of a normal early aEEG should not exclude indication of TH in infants with neurological evidence of moderate to severe HIE [54]. After the implementation of TH, the predictive value of aEEG has been evaluated. Chandrasekaran et al. found that persistently abnormal trace on aEEG at ≥ 48 hours of life was associated with adverse long-term outcomes and a systematic review [55] found that maximum predictive reliability was achieved at 72 h of life with a post-test probability of 95.7% (95% CI: 84.4 to 98.5%). Therefore, aEEG is a valuable tool in infants with HIE to be used for the classification of the level of encephalopathy and as a predictor of long-term outcomes. The persistence of elevated values of rScO2 was also associated with abnormal neuroimaging and adverse neurodevelopmental outcomes as low cerebral metabolism indicates low oxygen use, cerebral hyperperfusion and impaired autorregulation [56–58].*Preterm infants*: the incidence of seizures in preterm infants has been reported between 4 to 48%, and seizures were associated with adverse outcomes including IVH, white matter injury (WMI), cognitive impairment and neonatal death [13, 16, 59, 60]. The presence of SWC and continuous background pattern in the first week of life were associated to good neurodevelopmental outcomes, while absence of SWC and abnormal background activity were associated with neonatal death, severe IVH, WMI and neurological impairment at 2 years of age [61–64]. In extremely premature newborns during the first days of life, the occurrence of episodes of hypoxia/hyperoxia, hemodynamic and ventilatory instability, and systemic hypotension with decreased cerebral flow are common. For that, NIRS monitoring has been used extensively used in this population. A phase II randomized controlled trial conducted by the SafeBoosC Consortium evaluated newborns ≤ 72 h of life to demonstrate the feasibility and effectiveness of implementing continuous NIRS monitoring with a clinical management protocol. Neonates monitored with NIRS had lower burden of cerebral hypoxia or hyperoxia compared to controls and a trend towards lower IVH and mortality rates [65]. A hemodynamically significant patent ductus arteriosus (hsPDA) may be associated with increased pulmonary blood flow and decreased systemic blood flow. Chock et. al found that low renal oxygenation values (rSrO2), with rSrO2 < 66%, were associated with the presence of hemodynamically significant PDA [24]. Other studies have successfully demonstrated association between PDA closure and significant increases on cerebral and renal saturation [66, 67].*Other Applications*: ventilatory instability (respiratory acidosis/alkalosis), metabolic disorders, inborn errors of metabolism, cerebral malformations, stroke, congenital infections, sepsis, meningitis and need of extracorporeal circulation (ECMO) [48, 68, 69]. In 20% of infants with CHD electrographic seizures were detected, including repetitive seizures and status epilepticus [70]. Early recovery to normal aEEG background activity and presence of SWC was associated with good neurological outcomes after cardiac surgery [46, 71]. Perioperative electrical seizures were found in 30% of infants, of which only ¼ showed any clinical correlation. Failure to recover the background activity to a continuous pattern ≥ 48 h postoperatively was associated with neurodevelopmental delay. The persistence of abnormal aEEG for seven days after surgery was also highly associated with death [46].NIRS monitoring may help to evaluate efficacy or need for additional interventions such as ventilator changes, use of diuretics, change in prostaglandin (PGE) dose, need for blood transfusion or early surgical intervention. A rSrO2 < 30% was correlated with increased Intensive Care Units (ICU) stay, and rScO2 and rSrO2 < 45% and < 40% respectively, were correlated with need of ECMO and death [72]. NIRS monitoring was also useful to diagnose early renal insufficiency after surgical intervention [73–75].*Anemia and shock*: tissue oxygen delivery, somatic and cerebral saturations are directly affected by hemoglobin levels, especially in scenarios of important anemia, suggesting that NIRS monitoring may play a role in the indication of blood transfusion. A significant increase in rScO2 values was reported in children with rScO2 <55% treated with blood transfusion [76]. NIRS has also been demonstrated as a good early indicator of abnormal somatic perfusion and shock in different populations including newborns [77–79]. In the setting of shock, two site NIRS monitoring (cerebral and somatic) may be particularly useful in cases where autoregulation remains intact and somatic tissue oxygenation may be compromised earlier [80].

Implementation of a NeuroNICU requires specialized education, training, use of validated protocols and implementation of specific methodologies. Financial resources are needed for equipment, such as servo-controlled temperature and brain monitoring devices. Lack of specialized assistance and resources may result in inadequate interventions with possible lack of benefit or even harm to the patients. A systematic review found no reduction in mortality with the use of TH in LMIC countries [81] and possible reasons to justify this finding include inefficiency of the low technology cooling devices and lack of optimal care. Brain monitoring using conventional EEG requires skilled technologists, experienced neurologist interpretation which may not be readily available in many centers, especially for continuous bedside monitoring. aEEG and NIRS monitoring can be interpreted at the bedside but also requires training and experienced users [82, 83]. Unfortunately, the majority of neonatal units lack adequate longitudinal training, specialized staff, and access to all these resources, especially in LMIC. This is what motivated our group to consider telemedicine as a solution in this scenario.

Differently from the previous studies, the *PBSF Guidelines* (S3 Appendix) is unique for the use of an advanced telemedicine system to provide neurocritical care. The guidelines include continuous neuromonitoring with data recording and real time feedback from experts, provision of equipment and resources to the NICUs, and short- and long-term teaching to the professionals working at the units (S2 Appendix). Telemedicine has several applications including education, consultation, practice, and research [28]. This type of communication has shown results in continuing education among physicians and nurses, and has assisted healthcare professionals to improve health disparities, promoting access to specialized care [27, 29]. Live interactive audiovisual materials, such as live streaming video and viewing stored educational material, are important to deliver tele-education; it promotes opportunities for continuous learning and development by dissemination of information and training health-care professionals [26, 28]. Telemedicine may also be helpful in case discussions for decision making which is useful to promote interaction between physicians, nurses, and patients. Udeh et al. exemplified some benefits of telemedicine including [84]: a) promote evidence-based best practices through checklists and prompting; b) enhance monitoring, early identification, and treatment of critical illness; c) improve coordination of care; and d) increase night-time vigilance. The use of telemedicine in ICUs is associated with decreased mortality and length of stay [84, 85]. Surprisingly, telemedicine has not been used on a significant scale worldwide, although this methodology is low-cost, feasible, clinically useful, and sustainable. It could be even more useful in LMIC countries due to the limited structure and resources.

Brazil allows several opportunities for telemedicine implementation, expanding the actions of healthcare professionals and integrating healthcare services [86]. We developed the *PBSF Guidelines* with a surveillance and intelligence center to support clinical decisions across the country. Telemedicine has been used by our group in the past few years to promote educational training and remote neuromonitoring but its impact on clinical outcomes needs to be formally evaluated. Thus, results of this 3 years prospective, multicenter, and observational study will help to determine the incidence of neonatal problems associated with brain injury and disabilities, the incidence of clinical and subclinical seizures, detection of brain hemodynamic/oxygenation instability and associated interventions. The study will be limited to the 20 NICUs using the *PBSF Guidelines* and variability in clinical practices, experience of health care providers and staffing of the units, will be analyzed as it may affect some of the outcomes. Enrollment of such large number of patients will require a strong coordination between the central unit and all 20 centers, which has already been established by the CSI. Practical or operational issues will be to assure that all eligible patients are identified in a daily basis and approached for consent. Data collection requires careful training of data extractors and timely and precise data entry. A computerized and safe double-checking system has been developed. Biological signals will be continuously collected and stored at the CSI and multimodal signal analysis has been developed. Although low, there are costs for the implementation and use of the *PBSF Guidelines*. Thus, an adjusted analysis based on the profile of the units will be performed as costs might represent a limitation on the generalizability of the study findings. A future cost/benefit analysis is under planning.

